**Feasibility study of electronic screening and brief intervention for alcohol misuse in workplace settings**

**Protocol**

**Background**

*Alcohol-related harm and cost to the workplace*

Alcohol misuse (drinking above safe limits) is among the leading causes of preventable mortality and morbidity worldwide, with the highest death rates found in the European region ([1](#_ENREF_1)). In England in 2010, almost a quarter of adults (22%) aged 16 and above were drinking more than recommended weekly limits (26% men and 17% women) ([2](#_ENREF_2)), although a recent comparison of this survey data with sales data suggests around three quarters of the population are drinking above safe limits ([3](#_ENREF_3)). Alcohol-related harm is not limited to the individual drinker, it affects other people, society and the economy, making it the most harmful drug in the UK ([4](#_ENREF_4)). An estimated 11 to 17 million working days are lost annually in England due to alcohol-related sickness, with an additional 15 to 20 million days lost due to reduced employment. Lost productivity (caused by alcohol-related absenteeism, unemployment and premature death) costs the country up to £6.4 billion ([5](#_ENREF_5)), with total costs of alcohol-related harm to the health service and wider economy of £20 billion a year ([6](#_ENREF_6), [7](#_ENREF_7)). A recent study in the US has estimated a 4:1 benefit to cost ratio for organisations that implement screening, brief intervention and referral to treatment to address alcohol issues at work over 4 years ([8](#_ENREF_8)).

*Screening and brief intervention in a workplace setting*

Brief interventions are effective at reducing alcohol intake and are advocated by NICE as the first step in a tiered service for alcohol misusers ([9](#_ENREF_9)). However, the evidence to support their use is largely based on brief interventions delivered by health care professionals in primary care settings ([10-15](#_ENREF_10)). For brief interventions to comprise the population level approach needed to tackle alcohol misuse, the entire population needs to be screened ([16](#_ENREF_16)).

There are numerous barriers to implementing screening and brief intervention (SBI) in primary care ([17-21](#_ENREF_17)) and so it is important to consider the effectiveness of SBI in other settings, as recommended by NICE ([9](#_ENREF_9)). Most hazardous and harmful drinkers are of working age and do not seek help with their drinking, making the workplace an ideal setting for SBI, with access to individuals across a range of socioeconomic groups and ethnicities. SBI for alcohol misuse should be an integral part of health promotion activity within occupational health departments. SBI was found to be acceptable in a workplace setting (Scottish Local Authority), where 92% of respondents to a general lifestyle survey were happy to be asked about their drinking ([22](#_ENREF_22)). In 2009, a systematic review of workplace interventions for alcohol-problems identified four randomised controlled trials (RCTs), two from the US, one from Australia and one from Sweden. Although there was some indication that brief interventions and psychosocial skills training are effective in this setting, studies were fraught with methodological limitations including lack of exposure to the intervention, contamination of the intervention and controls obtaining access to the intervention ([23](#_ENREF_23)). The workplace setting presents barriers to delivering SBI, which will differ across organisations, thus introducing methodological challenges to conducting a trial, and suggesting the need for a feasibility study as a precursor to designing a definitive randomised controlled trial in this setting.

*Role of occupational health in tackling alcohol misuse*

The World Health Organisation recommends the provision of personal health resources, as one of the four ways of achieving a healthy workplace, which may include healthy food choices, campaigns to encourage physical activity, no smoking policies and health assessments ([24](#_ENREF_24)). There is some evidence on the effectiveness of health resources delivered in the workplace but this largely concentrates on physical activity (for which there is NICE guidance specifically for this setting ([25](#_ENREF_25))), diet and smoking ([24](#_ENREF_24)). The challenges facing SBI for alcohol misuse in the workplace setting may explain the lack of research in this field. Alcohol consumption is a sensitive topic. The perceived repercussions of divulging sensitive information in-person may affect self-reported veracity ([26](#_ENREF_26)). It is possible that employees will under report their alcohol intake in the workplace setting, where there may be concerns over the confidentiality of their responses. There is a limited literature on how employees feel about answering questions on their health in the workplace. There may be concerns that the information they provide may impact on their employment thus deterring employees from participating in such activities, or leading them to report less than they are actually drinking. Using the Internet to confidentially deliver screening and brief intervention may tackle some of the concerns employees may have with SBI in this setting.

*Online interventions for reducing alcohol intake*

The internet is increasingly used to deliver SBI with its advantages of scalability, instantaneous access, flexibility of use, and anonymity, which is important for a stigmatised behaviour like alcohol misuse. There is a growing evidence-base for these interventions, particularly in student samples, which has been demonstrated in the large number of systematic reviews in this field ([27-33](#_ENREF_27)). A recent systematic review of computer-based interventions for reducing alcohol intake found them to be as effective as in-person interventions, such as CBT and motivational interviewing, in a small number of studies ([27](#_ENREF_27)). Two of the 24 studies included in this review (but not in the meta-analyses) were based in a US workplace setting ([34](#_ENREF_34), [35](#_ENREF_35)). One study found personalised normative feedback (Check Your Drinking) to be more effective at reducing alcohol intake than assessment-only ([34](#_ENREF_34)). The other study had difficulties with recruitment related to employees’ privacy concerns and provided only preliminary support for electronic screening and brief intervention (eSBI) in the workplace ([35](#_ENREF_35)).

The Health on the Web (HOW) study, an online trial of eSBI for alcohol misuse, is currently underway in a large private organisation with almost 100,000 employees ([36](#_ENREF_36)). Employees were invited to take part in an online health check (including questions on alcohol consumption, smoking, diet and exercise) via the company web portal. A total of 3,375 participants completed the health screen in a three week period, 39% of which were drinking above recommended safe limits (scored five or more on the AUDIT-C) and as such were randomised to receive feedback on all health behaviours including alcohol consumption or feedback on all health behaviours except alcohol. All employees had access to the company web portal, therefore ensuring equity of access. A follow-up rate of 80% was achieved with email, postal and telephone reminders. The organisation had an active occupational health team that organised quarterly health campaigns for their staff, which were aimed at prevention and early identification rather than treatment. Campaigns included online information, facilitated monitoring activity, risk assessment, prizes for winners of competitions, road shows, health fairs, articles in the company newsletter and email reminders to take part. The organisation had worked with other academic institutions, which meant its employees were used to taking part in research and answering questions on their health. Other organisations, particularly in the public sector where less funding is available for health promotion activity, may not be as successful at recruiting and retaining participants to a study of this nature. Study participation may also be less acceptable in occupational settings where employees are not used to being asked questions about their health.

The proposed study draws on two innovations in brief intervention research: 1) the occupational health setting and 2) electronic interventions, both of which provide the opportunity to increase the scalability of SBI and a step towards a public health approach to tackling alcohol misuse. The few studies that have been conducted in this field to-date point to the challenges of providing SBI and eSBI in the workplace setting. This feasibility study will explore the barriers to delivering eSBI across six workplace settings. It will also determine the potential barriers to conducting a trial in this setting, for example whether the study process and the intervention are acceptable to employees, whether the intervention is suited to the level of need or if alternative resources are more appropriate. This feasibility study of eSBI in the workplace forms the preparatory work needed for a multi-site RCT and has been designed to inform an application to NIHR Public Health Research for a definitive trial to address the question ‘Is eSBI effective in workplace settings?’

**Aim**

To explore the feasibility and acceptability of offering electronic screening and brief intervention (eSBI) for alcohol misuse in workplace settings. This study will inform the design of a multi-centre randomised controlled trial of the effectiveness of eSBI in this setting.

**Objectives**

1. To undertake a feasibility study of online screening, personalised feedback and access to an extensive online alcohol intervention in six workplace settings in the South and North East of England.

2. To determine whether a definitive multicentre trial is feasible by estimating study parameters and thereby informing a sample size calculation. Study parameters include rates of eligibility, recruitment and retention at three months.

3. To explore the acceptability and potential perceived risk to employees of completing an online health screen, receiving feedback on health behaviours and access to an online alcohol intervention, and completing follow-up measures.

4. To determine the level of engagement with an extensive online alcohol intervention, and its suitability for this population.

**Study design**

A multi-site feasibility study of electronic screening and brief intervention for alcohol misuse for employees in six workplace settings in the South and North East of England.

**Ethical approval and research governance**

Ethical approval will be sought from UCL research ethics committee for all workplaces. Letters of approval are needed from each of the employers to support the ethics application. UCL will also be the sponsor of this research.

**Setting**

[name], director of the Alcohol Health Network, has approached several organisations across England with the offer of electronic screening and brief intervention for their employees as part of a feasibility study led by UCL and NCL. There has been considerable interest from both public and private sector organisations, which demonstrates, to some extent, the acceptability of this approach with employers and the need for this type of intervention in the workplace. This feasibility study has restricted inclusion to six organisations, which will allow for an exploration of differences between organisations in the number of eligible participants, mechanisms for recruiting participants and differences in acceptability among employees. Exploration of these factors will help inform the design of a definitive multicentre trial. Inclusion of more than six organisations was considered unethical due to the nature of a feasibility study, where the effectiveness of the intervention is yet to be established in this setting and is not the purpose of the study. The following organisations were selected for their diversity, as they include both public and private sector organisations, different types of public sector organisations (council, hospital, university), different sized organisations (ranging from 700 employees to 19,000) and different geographical regions (South and North East of England, rural and urban areas):

- Hospital (2,700 employees)
- University (2,900 employees)
- Local authority 1 (19,000 employees)
- Local authority 2 (5,218 employees)
- Local authority 3 (3,500 employees)
- Petrochemical manufacturer (700 employees)

Details of the health promotion activities within each organisation will be provided by the occupational health leads. Occupational health leads will update the study team on previous, current and future health promotion campaigns at steering group meetings.

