**Recruitment**

Occupational health leads will be consulted on the most suitable recruitment procedure for their organisation. Recruitment methods include: email, article on company web-portal or newsletter, or via posters. Occupational health leads will be asked to provide the reasons why they chose their preferred methods. Employees will be invited to complete an online health screen and to take part in a study led by researchers from UCL and NCL. If interested in learning more about the study, employees are invited to visit the study website, via hyperlink within emails, on web-portals or electronic newsletters. The study website will present the employee with participant information pages, which will explain the aim of the study, what will be involved if taking part, the potential advantages and disadvantages of participation and the implications of the findings. It will be made clear that taking part is voluntary, that their employer will not know whether they have taken part, and that all the information they provide will be anonymised (i.e. not linked with their name). If happy to take part, employees will be asked to complete an online consent form. On completion of the consent form, participants will be asked to complete the health screen (as detailed below).

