**Baseline data collection**

*Health screen*

Participants will be asked to answer questions of a range of behaviours known to impact on their health and wellbeing, namely alcohol, smoking, diet and physical activity. The 3-item AUDIT-C questionnaire will be used as an initial screen for alcohol misuse ([37](#_ENREF_37)), with a score of five or more indicating consumption above recommended limits ([36](#_ENREF_36)). The AUDIT-C comprises the first 3 consumption questions from the WHO Alcohol Use Disorders Identification Test (AUDIT) ([38](#_ENREF_38)). Questions relate to the frequency of alcohol consumption, quantity of alcohol consumed on a typical drinking day, and frequency of drinking more than 6 (women) or 8 (men) drinks on one occasion. For participants scoring 5 or more on the AUDIT-C, the remaining seven questions of the AUDIT will then be presented which focus on alcohol-related harm. Questions on smoking status, consumption of fruit and vegetables and level of physical activity will also be included in the health screen, using the same approach as the HOW study ([36](#_ENREF_36)).

*Demographics*

Participants will be asked to provide demographic information, consisting of gender, year of birth, ethnicity, occupational classification (categories to be supplied by the occupational health lead from each organisation). Participants will also be asked to provide an email address that will allow them to be contacted again in three months’ time. Demographic data will be collected at the end of the health screen, before provision of feedback on health behaviours.

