**Outcomes and outcome measures**

The outcomes will reflect the objectives of this feasibility study, which include 1) estimation of study parameters to inform the sample size calculation for a definitive multicentre trial; 2) acceptability and potential risk to employees of participation; 3) engagement with an extensive online alcohol intervention and its suitability for this population.

Outcome measures will include the AUDIT and a questionnaire designed by the research team that explores the acceptability and potential risk of delivering electronic screening and brief intervention to employees in the workplace. The questionnaire will also include questions on whether participants engaged with the online alcohol intervention (detailed below).

*Estimating study parameters*

For organisations that choose to recruit participants via email, rates of eligibility will be determined by the number of employees with a work email address as a percentage of the total workforce at each organisation. These data will be provided by the occupational health leads for each organisation. Occupational health leads will also provide information on the different types of jobs / occupational classifications within the organisation, and which of these require a work email address. This information will highlight any inequalities introduced by restricting inclusion to those employees with a work email address. The number of employees who complete the health screen (and therefore consent to participate in the study) will be reported as a percentage of the total number of employees invited to participate in the study via email, for each organisation. The number of participants scoring five or more on the AUDIT-C will be reported as a percentage of those who have completed the health screen. Finally, the number of participants who complete follow-up questionnaires at three months will be reported as a percentage of those participants completing the health screen, for each organisation.

*Acceptability and potential risk*

The follow-up questionnaire will ask participants about the acceptability of answering questions on their health and receiving feedback online in a workplace setting. There are questions on use of technology, sensitivity of questions, time taken to participate at work and the confidentiality of responses. Participants will be asked if they have any concerns with this approach, including the possible harm to the employee.

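### The protocol records no route of arrival, so at a site using several recruitment channels completers cannot be allotted to a channel and the email recruitment rate takes in people who came another way

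*Protocol*

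**What the plan says.** All references are to the protocol.

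- **Setting.** Six organisations are included so that differences between them can be explored in three respects: numbers eligible, "mechanisms for recruiting participants and differences in acceptability among employees". The use is stated: "Exploration of these factors will help inform the design of a definitive multicentre trial".
- **Recruitment.** The method is settled site by site: "Occupational health leads will be consulted on the most suitable recruitment procedure for their organisation". The options are listed as "Recruitment methods include: email, article on company web-portal or newsletter, or via posters", and nothing limits a site to one. About the choice itself, "Occupational health leads will be asked to provide the reasons why they chose their preferred methods". Employees reach the study website "via hyperlink within emails, on web-portals or electronic newsletters".
- **Baseline data collection.** Participants give "demographic information, consisting of gender, year of birth, ethnicity, occupational classification", and an email address for follow-up. Route of arrival is not listed.
- **Outcomes and outcome measures.** The recruitment rate is the number of employees who complete the health screen "as a percentage of the total number of employees invited to participate in the study via email, for each organisation". The numerator is not limited to people who came through the email. For email sites the section also plans work-email coverage of the workforce and a description of which jobs require a work email address.

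**The concern.** How employees are invited is one of the choices the definitive trial must make, and the protocol says this study will help with it. To learn anything about a channel, one must know which participants it brought in. If a site sends an email, posts a portal article and puts up posters, the data described will show one pooled count of completers.

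The same gap reaches a named study parameter. Recruitment is among the rates in Objective 2, and the Analysis section uses it to help judge whether a definitive trial is feasible. At a multi-channel site the numerator covers every channel and the denominator only one. The percentage is then neither the response to the email nor the uptake in the workforce.

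**Working it through.** The protocol gives no figure on this point to reproduce. The check has three parts.

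**1. Is route captured anywhere?**

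| Place in the protocol | What is collected | Route of arrival? |
|---|---|---|
| Recruitment | Each site's preferred methods and the lead's reasons | Site level only |
| Baseline data collection | Health screen, four demographic items, email address | No |
| Follow-up data collection | Unique ID, secure storage | No |
| Outcomes: acceptability | Technology, sensitivity, time, confidentiality, concerns | No |
| Outcomes: engagement | Down Your Drink registration, logins and pages | No; this is traffic on the intervention site, not arrivals at the study website |

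**2. What would recording it make estimable?** Take six sites and three method groups (email; portal or newsletter; poster). Compare the rank of the design matrix with site indicators alone and with method indicators added. The protocol assigns no methods to sites, so the patterns are assumed.

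| Pattern | Rank, site only | Rank, site + method | Method contrasts within site |
|---|---|---|---|
| One method per site | 6 | 6 | None, whether or not route is recorded |
| All sites use all methods, route recorded | 6 | 8 | Both |
| Two sites mix methods so that all three are linked, route recorded | 6 | 8 | Both |
| Sites mix methods, route not recorded (protocol as shown) | 6 | not constructible | None: participants cannot be assigned to a method |

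The maximum rank is 6 + 3 − 1 = 8. Recording route therefore helps exactly where some sites use several channels.

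**3. Effect on the recruitment percentage.** Let E be employees emailed, C all completers and A completers who came by another route.

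- Rate as defined: C / E.
- Rate for email arrivals: (C − A) / E.
- Ratio: C / (C − A) = 1 / (1 − s), with s = A / C.

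Illustration for the hospital (2,700 employees). Assume that 60% have a work email, so E = 0.60 × 2,700 = 1,620. Assume the uptake seen in the Health on the Web study described in the Background: 3,375 / 100,000 ≈ 3.4%, so C = 2,700 × 0.03375 ≈ 91. That company had almost 100,000 employees, so the uptake is approximate. The 60% and the values of A are pure assumptions.

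| A (assumed) | s | As defined, C/E | Email arrivals, (C − A)/E | Ratio |
|---|---|---|---|---|
| 10 | 11% | 91/1,620 = 5.6% | 81/1,620 = 5.0% | 1.12 |
| 30 | 33% | 5.6% | 61/1,620 = 3.8% | 1.49 |
| 45 | 49% | 5.6% | 46/1,620 = 2.8% | 1.98 |

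The ratio depends only on s, not on the assumed uptake or email coverage.

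**Precision.** At the planned minimum of 30 per site, the 95% half-width 1.96 × √(p(1 − p)/30) is 17.9 points at p = 50%, 17.5 at 39% and 14.3 at 80%, before any split by channel. Channel results can only be descriptive.

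**The case against.** The strongest reply is that the Setting section promises an exploration of differences between organisations, not the yield of a method independent of organisation. Comparing methods is not among the numbered objectives, and the analysis is described as largely descriptive. Knowing which methods each site chose and why, together with the planned information on email coverage, already allows a site-level account. All of this stands. A reader might infer that the six-site design fails one of its stated purposes, or that the leads' reasons are all that will be known about mechanisms. The document supports neither inference.

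A second reply is that recording route does not separate method from organisation if each site uses a single method. This also stands, as the rank check shows. All six sites might even choose email alone, and then there is no contrast to make.

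Third, attribution is imperfect. One employee may see an email, a poster and a portal article, and the link used is only the last of these. Portal, newsletter and poster have no defined denominator, so they yield counts and not rates. This limits what the field can show but does not make it worthless.

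Fourth, the full questionnaires and the SAP are not at hand, so the statement is that no item appears in the protocol as shown. Tabulation by channel could be left to a SAP. Capture of the field could not, because an analysis plan cannot recover what was never collected.

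**Conclusion.** The point holds in a limited form. At any site using more than one channel, completers cannot be allotted to a channel from the data described, and the email recruitment percentage includes arrivals by other routes. The inflation is 1/(1 − s): about 1.1 if a tenth of completers come by other routes, about 1.5 if a third do, and 2 if half do. The protocol gives no value for s. Where every site uses email alone, s is zero and the problem disappears.

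The conclusion rests on two readings: that sites may combine methods, which the Recruitment section permits, and that the numerator is all completers, which is how the Outcomes section words it.

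A reader might go further and conclude that recording route would remove the confounding of method with organisation. It would not, except through sites that mix methods. Nor can expected numbers per channel be predicted. The Background itself cautions that the uptake in the earlier company may not carry over to other organisations. This is a cheap improvement to data capture in a descriptive study, not a flaw that undermines it.

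**What to change.** 1. **Recruitment section.** Give each channel at each site its own web address, including a short one printed on posters. Alternatively, add one item before the health screen asking how the employee heard of the study. Store the answer with the unique ID. Log the methods used at each site and the date of each mailing or posting.
2. **Outcomes section.** Report completers, and the percentage scoring five or more on the AUDIT-C, by channel within each organisation. Give plain counts of completers where a channel has no denominator. Present the email recruitment rate as now defined and again with the numerator limited to email arrivals.
3. **Analysis section.** State that channel comparisons are descriptive, and that where a site uses a single method, method remains confounded with organisation.

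Cost: distinct links need a little set-up on the study website and no extra staff. The tick-box adds one field for participants. Either way, attribution stays imperfect for employees who see several channels, and the report should say so. The change has to be made before recruitment opens.
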